### Ethics Approval

This study protocol has been approved by the National Ethics Committee for Health Research in Cambodia (reference number 105 NECHR) and by the Institutional Review Board of Institute of Tropical Medicine (Antwerp; reference number 1323/19). The study is also registered as part of the SCUBY protocol at the International Standard Randomised Controlled Trials Number (ISRCTN) registry, number ISRCTN41932064 (first date of publication February 3, 2020).

## Results

Data collection was carried out from mid-July to mid-October 2020. By June 2021, the data cleansing process was finished and cleaned data were properly managed as data sets. As of December 2021, the recruitment process was completed, with 5072 eligible individuals participating in the data collection; however, data analysis is pending. Results are expected to be fully available in mid-2022.

## Discussion

This protocol aims to assess the performance of the 3 dominant care models for T2D and HT through the cascade of care framework, using the population-based survey. This framework will allow us to identify the leakages in the system and the unmet need for care [24]. In addition, we will be able to better understand the diversity in service models across the country by comparing 3 different care models. The design of this study, using large-scale primary data, is unique. The evidence generated from this large-scale survey of more than 5000 households will stimulate policy-relevant analysis that is informative to the existing care for T2D and HT provided by the 3 main care models and act as baseline data for progress monitoring purposes [24]. Identifying gaps in the health system is vital to improve efficiency and effectiveness of its performance.

The strengths of the study are primary data collection, a large sample size, and multiple types of data. This allows us to assess multiple outcomes and to link them with other indicators such as health care utilization, health seeking behavior, morbidity profile, and sociodemographic characteristics. The limitations relate to its complicated set up. The multilevel stratification and the collection of multiple types of (outcome) data make the research design and practical organization difficult. The clustering on more than 2 levels and the different outcomes make it challenging to calculate an ideal sample size following all regulations. We have addressed this by seeking optimal balance between maximizing precision and minimizing costs for feasibility. The purposive selection of ODs based on the mapping of existing care models limits the generalizability of results. However, through randomization within ODs, we will strive for maximum internal validity.

Despite these limitations, this study protocol has a large potential to produce evidence of the performance of different care models for T2D and HT in Cambodia. These insights will help implementers and policy makers to assess scale up and adapt strategies. This is of vital importance owing to the increasing burden of CVDs, T2D, and HT in the country [5,12,13]. As many LMICs struggle with similar burdens of disease and similar structural problems in their health systems, the study protocol and its expected results are also useful for monitoring and scaling up of care for highly prevalent chronic diseases across the globe.

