## Methods

### Study Design

This study protocol is part of a larger population-based survey—the SCUBY (Scale up diabetes and hypertension care for vulnerable people in Cambodia, Slovenia and Belgium) project [28], which includes other substudies focusing on (1) the health status of people aged 40 and over and the existence of comorbidities, (2) health care utilization and health care expenditure among people aged 40 and above and people living with T2D or HT or both, (3) the lifestyle and knowledge of T2D and HT among people living with T2D or HT or both, and (4) the self-management and social support for people living with T2D or HT or both.

To meet the aforesaid specific aims, 5 operational districts (ODs) in different provinces will be purposefully selected out of 103 ODs across the country. The selection is based on a mapping exercise conducted in the SCUBY project. Only in the OD Daunkeo the 3 care models coexist. The OD Samrong in a bordering province hosts a typical noncommunicable disease (NCD) clinic at the referral hospital (the WHO PEN and Peer Educator Network are not there yet). The OD Kong Pisey does not have the WHO PEN and the NCD clinic at the referral hospital (only the Peer Educator Network of MoPoTsyo exists—with relatively strong network). The OD Pearaing is one of the ODs piloting the WHO PEN and started implementing the program since 2015. At the time of study, 8 of 9 health centers have implemented the WHO PEN. The OD Sotr Nikum is historically and significantly influenced by the financial aid of various development partners and nongovernmental organizations—contextual factor is a focus. The referral hospital in this OD has a Chronic Disease Clinic, where people with T2D or HT or both and those with HIV seek treatment and care [29]. At the time of study, 5 of 25 health centers have implemented the WHO PEN. Table 1 shows the existence of care provision for T2D and HT in each OD.

**Table 1 table1:** Selected provinces and ODs^a^ with different types of care models.

OD name	Province	Existing care provision	Care model
Samrong	Oddar Meanchey	NCD^b^ clinic at the referral hospital	Hospital-based care
Pearaing	Prey Veng	NCD clinic^c^ + WHO PEN^d^ (high coverage)	Health center–based care
Sotr Nikum	Siem Reap	NCD clinic^c^ + WHO PEN (low coverage)	Health center–based care with context
Kong Pisey	Kampong Speu	Peer Educator Network^e^	Community-based care
Daunkeo	Takeo	NCD clinic + WHO PEN + Peer Educator Network	Coexistence of care

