### Sampling and Sample Size

This population-based survey follows a multistage stratified random cluster sampling [30]. For the sampling procedure, each OD is considered as a stratum due to the care model present (Table 1). Based on rules of stratification, each stratum is theoretically independent from one another, and its selection can be based on the aforementioned specific aims [30]. In each stratum, clusters of primary sampling units (villages) will be randomly sampled.

Based on the multistage stratified random cluster sampling, 3 stages of stratification are applied, and in each stage randomization is employed. ODs are the strata, and health centers impacted by the types of care models are selected. For the first stage of stratification, sampling with equal probability (equal probability selection method) will be used to determine the number of villages under the catchment areas of the impacted health centers in each OD. This equal selection is also made to ensure oversampling for some ODs. If using proportionate allocation of the sample units across the ODs, the sample selected from the ODs representing certain types of care models would be too low to have enough statistical power for the analyses. In this survey, disproportionate allocation is done to randomly select equal-sized samples in the 5 ODs [30]. For the second stage of stratification, households having adult(s) aged 40 and above (secondary sampling units) in the selected villages are selected and listed. Systematic random sampling is used to select the households from each village. For the third stage of stratification, only 1 individual meeting the eligibility criteria (described later) is randomly selected from each household to reduce the clustering effect. Thus, 1 eligible individual is selected from each household, making the total sample size of eligible individuals the same as the sample size of households (Figure 1).

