The population in the catchment areas is not confined to seek care only in the designated public health facility. To address this, we will also collect patient registry data from the public health facilities in the study setting with regard to patients receiving treatment for triangulating the care model selected.

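### Random sampling within districts gives no internal validity to the care-model comparison, because care model is aliased with a few purposively chosen districts

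*Protocol article*

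**What the plan says.** All places are in the protocol article.

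- **Choice of districts (Study Design).** "5 operational districts (ODs) in different provinces will be purposefully selected out of 103 ODs across the country". Table 1 gives hospital-based care to Samrong, community-based care to Kong Pisey and coexistence to Daunkeo ("Only in the OD Daunkeo the 3 care models coexist"). Health center-based care goes to Pearaing and, with the added tag of context, to Sotr Nikum. Sampling and Sample Size makes each OD a stratum because of the care model it hosts.
- **Randomization (Sampling and Sample Size).** Villages, then households, then one eligible person per household are drawn at random within each OD.
- **Comparison (Introduction; Statistical Analysis Plan).** Aims 3 and 4 compare the diabetes (T2D) and hypertension (HT) cascades between care models 1 to 4. Care model setting is also a candidate term in the logistic regression.
- **Validity (Discussion).** The stated limitation of purposive selection is generalizability. The answer offered is: "However, through randomization within ODs, we will strive for maximum internal validity".
- **Frame (Sampling and Sample Size; Study Design).** "ODs are the strata, and health centers impacted by the types of care models are selected", and villages come from the catchments of those centers. For Sotr Nikum, "5 of 25 health centers have implemented the WHO PEN"; Table 1 describes that OD as having low WHO PEN coverage.

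**The concern.** Random sampling and random allocation protect against different errors. Sampling at random within Samrong lets the Samrong sample stand for the sampled part of Samrong. It does not make Samrong exchangeable with Kong Pisey or Daunkeo apart from the care model. The Discussion answers a confounding problem with a sampling device and admits only a limit on generalizability.

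This matters because the article promises evidence on the performance of the care models for scale-up decisions. A reader who accepts the internal-validity sentence will take a difference between two districts, in different provinces and with different histories, as the effect of the model each one hosts.

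A second, smaller matter is what the Sotr Nikum sample represents, if villages were drawn only around the health centers that run WHO PEN.

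**Working it through.** **1. The plan's own figures.** n = 1.96² × 0.1 × 0.9 × 1.5 × 1.2 / (0.24 × 4.6 × 0.01²) = 0.62234 / 0.0001104 = 5637, as stated. The fielded sample is 24 × 44 = 1056 per OD and 5 × 1056 = 5280 in total, also as stated. Neither figure is in dispute. They fix the number of households within ODs and leave the number of ODs at five.

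**2. Degrees of freedom at the level where care model varies.**
- Five Table 1 labels: 5 ODs − 5 labels = 0 residual.
- Four models in the aims, pooling Pearaing and Sotr Nikum: 5 − 4 = 1 residual. That one comes from a pair with coverage of 8/9 = 89% and 5/25 = 20%, one of which was chosen with donor context in mind.

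More villages or households do not change either count.

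**3. Covariates.** The regression lists age, sex, marital status, education, wealth quintile and health care utilization. For the later bars it adds BMI, lifestyle, knowledge, self-management and social support. These vary between persons and households. A feature that takes one value per OD, such as the aid history that Study Design names for Sotr Nikum, cannot be separated from care model by adjusting for them.

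**4. Illustration of size.** Assume no care-model effect, a true bar of 50%, and OD differences from other causes with standard deviation s. The article gives no value for s; 3 and 5 points are assumed. The within-OD variance of a difference is v = 2 × 1.5 × 0.25 / n, where 1.5 is the protocol's design effect. The rejection rate of a nominal two-sided 5% contrast is 2 × [1 − Φ(1.96 × √v / √(v + 2s²))].

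| Cases per OD | √v (points) | s = 3 | s = 5 |
|---|---|---|---|
| HT, 300 (assumed) | 5.00 | 13.5% | 26% |
| HT, 150 (1056 × 14.2%) | 7.07 | 9% | 17% |
| T2D, 101 (5072/5 × 10%) | 8.62 | 8% | 13% |

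The 14.2% is the national figure for ages 18 to 69 in the Introduction and is used here only as a low value.

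**5. Sotr Nikum frame.** If the affected centers are the WHO PEN centers, 44 villages come from 5 catchments (44/5 = 8.8 per center), and the other 20 of 25 centers (80%) lie outside the frame. The sample would then describe PEN catchments, while Table 1 labels the OD by its low overall coverage.

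**The case against.** The comparison is openly observational and the ODs are fixed, purposively chosen strata. The sentence says only that the authors strive for internal validity. Sotr Nikum's context is flagged. The article also acknowledges care sought elsewhere ("The population in the catchment areas is not confined to seek care only in the designated public health facility") and plans registry data to triangulate. All of that is true, and cascades described OD by OD remain sound. None of it deals with differences between ODs that coincide with the care model.

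Several stronger readings are tempting, but the document does not support them:

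- **That confidence intervals are too narrow whatever the question.** For a difference between these five named ODs, leaving out between-OD variance is correct. The rates in the table apply only when the contrast is read as a care-model effect. Simple random sampling errors would raise them to 17% and 33% (300 HT cases) or 9% and 17% (101 T2D cases), but that ignores the protocol's own design effect.
- **That any difference in wealth or access will pass as model performance.** Wealth and utilization are planned candidate covariates. The OD-level remainder is the problem.
- **That Sotr Nikum is certainly sampled only around its 5 PEN centers.** This is the natural reading, but the article does not define which centers count as affected.
- **That a high-versus-low coverage contrast fails.** None is planned; coverage is a descriptor in Table 1. An OD-wide bias of (1 − 5/25) × 20 = 16 points would rest on an invented 20-point gap and on equal catchments.
- **That every care model has a single OD.** Health center-based care has two. Their difference is still a poor yardstick for OD variation: it is one pair, with sampling error, and one member has unusual donor context.
- **That the bars should be split by reported provider.** This depends on questionnaire items not shown.

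**Conclusion.** The internal-validity sentence is wrong as it bears on aims 3 and 4. Care model is wholly aliased with OD under the Table 1 labels and almost wholly under the four models of the aims. The conclusion follows from the design alone and needs no assumed figure.

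The rejection rates of 8% to 26% against a nominal 5% only illustrate the possible size. They depend on the assumed between-OD SDs, a bar at 50% and, for HT, the assumed number of cases.

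The Sotr Nikum point is conditional: the frame and the label need to be reconciled, and on the natural reading the label does not fit the people sampled.

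**What to change.** 1. In the Discussion, limit the sentence to the claim that random sampling within ODs makes each sample represent its sampled area. Add that care model coincides with OD and province, and state OD-level confounding as a limitation beside generalizability.
2. Report the results of aims 3 and 4, and the care model setting coefficient, as differences between the selected ODs and not as care-model effects.
3. State which health centers counted as affected in each OD. If Sotr Nikum was sampled only in its 5 WHO PEN catchments, label its results as PEN catchments (5 of 25 health centers) rather than as a low-coverage OD. Base its first-stage weight on the villages in those catchments.

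Data collection has ended and the article reports analysis as pending, so no new data are needed. The cost is some wording, possibly one weight base, and a more modest conclusion.

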## Appendix

Multimedia Appendix 1 Questionnaire about household information.

Multimedia Appendix 2 Questionnaire about eligible individual information.

Multimedia Appendix 3 Sample list of the eligible households in each village.

Multimedia Appendix 4 Sample record book of anthropometric and biochemical measurements of all the eligible individuals.

Multimedia Appendix 5 Sample record book of HbA_1c_ and Creatinine measurements of known T2D patients or the eligible individual having FBG ≥126 mg/dl.

Multimedia Appendix 6 Identified explanatory variables.

## Abbreviations

CVD: cardiovascular disease
FBG: fasting blood glucose
HbA_1c_: glycated hemoglobin A_1c_
HT: hypertension
LMIC: low- and middle-income country
NCD: noncommunicable disease
OD: operational district
PHC: primary health care
SCUBY: Scale up diabetes and hypertension care for vulnerable people in Cambodia, Slovenia and Belgium
STEPS: STEPwise approach to NCD risk factor surveillance
T2D: type 2 diabetes
WHO PEN: World Health Organization Package of Essential Noncommunicable Disease Interventions
